#### Blinding

Treatment allocation is by definition un-blinded, but since the hospital based reactivation care program is in fact the usual care provided in the intervention hospital it is possible to maximize blinding of data collectors by describing the three offered health care programs as usual care in all communications, thereby concealing treatment allocation. Furthermore, blinded analyses of data will take place when possible.

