### Data collection

There is no clear consensus on the time period during which effects of interventions on physical functioning and quality of life will be maintained. In some studies effects were present at six to twelve months after the start of the intervention, with the largest effect present around three months [24,26]. Therefore, main data collection of patient and caregiver outcomes takes place at time of hospital admission (T0), three months after hospital admission (T1) and twelve months after hospital admission (T2). Trained research nurses and students will administer questionnaires to patients by means of interviews at T0, T1 and T2. Furthermore, informal caregivers will receive paper questionnaires sent by mail. Patient and caregiver outcome measures will then be compared between the three hospitals. In addition a survey is administered among personnel of the three hospitals at one time during the second half of the inclusion period. Additional triage, outcomes, process, and cost information is collected from patient files and hospital ICT systems at time of discharge, during the intervention and in retrospect. Based on the pilot results we expect around 60% of patients analysable at 3 month follow up. Loss to follow up is minimized by making house calls and interviewing the patients in person [51]. Tables 1, 2, 3, 4 and 5 show a complete overview of outcome variables and data collection instruments for demographics and triage (table 1), effect evaluation (tables 2 and 3), process evaluation (table 4) and cost evaluation (table 5).

**Table 1 T1:** Data collection of patient and informal caregiver: demographics and triage

Evaluation	Variables and+ instruments	Data collection methods	Data collection times			**Notes**:
			**T0**	**T1**	**T2**	

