##### Demographics

Data on demographics (e.g. age, socioeconomic status, marital status, and gender) is gathered at T0, T1 and T2 by means of the Minimal Data Set (MDS) and hospital registries. The MDS is developed in light of the national program elderly care in the Netherlands and aims to compare elderly persons as well as their caregivers participating in different projects in the Netherlands by measuring demographics, quality of life, ADL functioning, experienced health and health care utilization (patient-level) as well as demographics, experienced health and burden of care, quality of life, and objective burden of care (informal caregiver level). The MDS is a combination of (parts of) validated questionnaires and is administered by trained research nurses and trained students (e.g. medical students or other students who have experience with research and/or elderly care), who interview patients at T0, T1 and T2. The data is collected from informal caregivers by means of mailed paper questionnaires, which are self-administered by informal caregivers and then sent back to researchers. A reminder including an extra copy of the questionnaire is sent to informal caregivers if they did not send back the first questionnaire. Additional data on demographics as well as data for other elements of the evaluation (e.g. medication, diagnosis, specialist consults) is collected from medical registries after hospital discharge.

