#### Effect evaluation (tables 2 and 3)

All outcome data of the patient are collected by the same means as the MDS described above.

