##### Process of care (patients)

Patient experiences with delivered care are measured at T1 by means of the Patient Assessment of Chronic Illness Care (PACIC) questionnaire, and consists of questions on care received in the last 3 months [74]. In addition, specific experiences with hospital care delivered during total hospital stay around T0 are measured with the (Hospital) Consumer Assessment of Healthcare Providers and Systems ((H)CAHPS), which consists of questions on treatment by nurses and doctors, hospital environment, experiences with hospital stay as well as discharge from the hospital, and general appreciation for the hospital [75]. Registering process indicators involves a continuous measurement of the care provided to the elderly and their caregiver. At this time it does not appear possible to make use of an Electronic Patient Dossier (EPD) in all three hospitals. Therefore, process indicators will be collected partly from existing registrations. The remaining indicators are collected by research nurses and students. Insight into the care process is provided by covering the topics of 'determining vulnerability'; 'provided medical care (diagnostics and treatments)' and 'the extent of multidisciplinary meetings'.

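### The Blinding section claims that a usual-care label conceals allocation; it cannot conceal the centre contrast in the nested trial and only partly masks the cohort comparison

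*Protocol article*

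**What the plan says.** The Blinding section opens with a concession: "Treatment allocation is by definition un-blinded". It then reasons that the programme is the ordinary care of the intervention hospital, so that blinding of data collectors can be maximised by "describing the three offered health care programs as usual care in all communications, thereby concealing treatment allocation". It adds that data will be analysed blind when possible.

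Other sections say who collects what:

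- Data collection: "Trained research nurses and students will administer questionnaires to patients by means of interviews at T0, T1 and T2". Follow-up is in person, with house calls.
- Effect evaluation: "All outcome data of the patient are collected by the same means as the MDS described above". Under Demographics, the Minimal Data Set (MDS) "is administered by trained research nurses and trained students".
- Process of care (patients): PACIC asks about care in the preceding three months. The section continues: "In addition, specific experiences with hospital care delivered during total hospital stay around T0 are measured with the (Hospital) Consumer Assessment". Table 4 places both instruments in the T1 patient interview.
- The same section, on process indicators that existing registrations do not supply: "The remaining indicators are collected by research nurses and students". The topics named include care provided and the extent of multidisciplinary meetings.
- Tables 2 and 5 list patient interviews on (re)admission and care use at T1 and T2.

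**The concern.** The Blinding section states a protective property as a consequence of a communication rule. A reader of the results would rely on it when judging Katz-15, SF-20, EuroQol and GDS-15, which are obtained by interview, and the Short Physical Performance Battery (SPPB), a test that the patient performs in front of the assessor. All of these leave room for probing, scoring and encouragement. The abstract says that higher levels of integrated care are expected to do better, so an assessor who knows the group and shares that expectation could move scores that way. Analysing the data blind does not remove a shift already in the recorded scores.

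The question is therefore whether calling every programme usual care can hide allocation in each of the two comparisons, given what interviewers see and ask.

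**Working it through.** **The plan's own figures.** The only computed figures are the cohort powers, based on Katz-15. With SD 1 and a two-sided 5% test (assumed, since alpha is not stated), power is about Φ(d/√(1/n₁ + 1/n₂) − 1.96).

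- 300 v 733, d = 0.25: 0.25/0.0685 = 3.65, power 95.4% (stated 95%).
- 300 v 733, d = 0.20: 0.20/0.0685 = 2.92, power 83.1% (stated 83%).
- 600 v 733, d = 0.20: 0.20/0.0551 = 3.63, power 95.3% (stated 95%).

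The figures reproduce. They identify Katz-15, an interview outcome, as the basis of the sample size, but neither support nor undermine the blinding claim. That has to be checked by setting the sections side by side.

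**Nested trial.**

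1. Evaluation design and Population: eligible patients in the intervention hospital are randomised to the programme with a centre stay (n = 200) or without one (n = 200).
2. Both arms therefore share one hospital and one programme name. A label common to three hospitals takes the same value in both arms and carries no information about the randomised contrast, but neither does it hide it.
3. A centre stay lasts at most three months (Description of the program) and follows the hospital stay (Setting). T1 is three months after hospital admission. If the hospital stay lasts L days, a full-length centre stay ends at L days plus three months. Inclusion requires more than 48 hours in hospital, so L is above 2 days and a full-length stay outlasts T1. How many patients stay that long is not stated.
4. Evaluation design names three months as the time at which the effect of the centre stay is measured, and follow-up is face to face. For some patients the place of the visit may itself show the arm.

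**Cohort.**

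1. Setting: the comparison is between three hospitals, so hospital is the exposure.
2. T0 takes place within 48 hours of admission. Whoever interviews then knows the hospital, and hence the group, whatever the programme is called.
3. What the label can hide is which of the three programmes is the one under test.

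**What follow-up interviewers hear.** At T1 the patient interviews include PACIC, (H)CAHPS, (re)admission and care use as well as the outcome scales. Answers about the last three months, hospital discharge or a residential stay can reveal hospital or arm. The article gives no order of items and does not separate outcome assessors from collectors of process data.

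**What is not exposed.** Mortality comes from medical registries, and caregiver quality of life and burden come from mailed questionnaires. The patient interviewer does not touch these.

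**The case against.** The case for the article has several parts.

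- *The section is hedged.* It says that allocation is un-blinded and speaks of maximising blinding. This stands: the article does not present itself as fully blinded. But the sentence ends by asserting concealment, and that assertion is at fault.
- *The label does something.* Bias towards the expected result needs an assessor who knows which group should do better. Knowing the hospital does not by itself supply that. This stands for the cohort, so it would be wrong to say that the label conceals nothing there. It does not help the nested trial.
- *Same staff, same sitting.* A reader might infer that one interviewer meets a patient at T0, collects that patient's process data and later scores the outcomes, all T1 items being asked together. The documents show shared staff categories only. They name neither individuals nor sittings, and Table 4 lists process indicators under medical registers, so only an unnamed remainder passes through these staff. The inference is possible but unsupported.
- *Size.* A reader might put a figure on the bias. An assumed interviewer shift of 0.05 to 0.15 SD would be 20% (0.05/0.25) to 75% (0.15/0.20) of the planned effect. Nothing in the documents supports that range, the quotient only restates the assumption, and 0.20 to 0.25 SD belongs to the cohort, not the nested trial. It should not be used.
- *Field detail.* A condensed article may leave item order and rostering to the full protocol. Agreed: their absence is not the point. The point is a stated property that the described design lacks.

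**Conclusion.** The concern holds in a limited form. Concealment of allocation from data collectors does not follow from the usual-care label. In the nested trial the label cannot bear on centre versus no centre. In the cohort it gives at most partial masking, as to which programme is under test. The statement matters for the interviewer-obtained outcomes (Katz-15, SF-20, EuroQol, GDS-15, SPPB) and not for registry mortality or mailed caregiver questionnaires.

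The size and even the presence of any resulting bias are unknown. The conclusion rests on the contrast, timing and collection methods that the article describes. It needs no assumption that the same individual sees a patient throughout, or that every assessor learns the arm. It should be corrected, but it does not invalidate the design.

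**What to change.** 1. In the Blinding section, replace the closing claim of concealment with a statement that outcome assessment is not blinded to centre stay in the nested trial, and is only partly masked in the cohort (as to which programme is under test).
2. At T1 and T2, administer Katz-15, EuroQol, SF-20, GDS-15, MMSE and SPPB before PACIC, (H)CAHPS, (re)admission and care-use items, wherever those are scheduled.
3. Have the interviewer record whether hospital or arm was known.
4. Interpret interviewer-based outcomes alongside registry mortality and the mailed caregiver questionnaires.

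The cost is one sentence, a reordered questionnaire, one extra item and a paragraph of interpretation. Item order reduces unmasking by the questions themselves; it cannot mask a patient who is still at the centre at T1, which is why the corrected statement and the recorded item are needed as well.

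Using a different interviewer at T1 and T2 is optional where existing rosters allow. With 1,100 patients in the intervention hospital and 500 to 600 in each of two control hospitals (1,100 + 2 × 500 = 2,100 to 1,100 + 2 × 600 = 2,300) and house calls, it is not clearly cheap, and patients would lose continuity of interviewer.

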### Data collection

There is no clear consensus on the time period during which effects of interventions on physical functioning and quality of life will be maintained. In some studies effects were present at six to twelve months after the start of the intervention, with the largest effect present around three months [24,26]. Therefore, main data collection of patient and caregiver outcomes takes place at time of hospital admission (T0), three months after hospital admission (T1) and twelve months after hospital admission (T2). Trained research nurses and students will administer questionnaires to patients by means of interviews at T0, T1 and T2. Furthermore, informal caregivers will receive paper questionnaires sent by mail. Patient and caregiver outcome measures will then be compared between the three hospitals. In addition a survey is administered among personnel of the three hospitals at one time during the second half of the inclusion period. Additional triage, outcomes, process, and cost information is collected from patient files and hospital ICT systems at time of discharge, during the intervention and in retrospect. Based on the pilot results we expect around 60% of patients analysable at 3 month follow up. Loss to follow up is minimized by making house calls and interviewing the patients in person [51]. Tables 1, 2, 3, 4 and 5 show a complete overview of outcome variables and data collection instruments for demographics and triage (table 1), effect evaluation (tables 2 and 3), process evaluation (table 4) and cost evaluation (table 5).

**Table 1 T1:** Data collection of patient and informal caregiver: demographics and triage

Evaluation	Variables and+ instruments	Data collection methods	Data collection times			**Notes**:
			**T0**	**T1**	**T2**	

**General**						
Patient	**Demographics**					
	MDS (age, ethnicity, SES, education)	Interview patient	**X**	**X**	**X**	Partly at T1 and T2
		Patient hospital files	**X**			incl info hospital ICT
Informal caregiver	**Demographics**					
	MDS (relation to patient, SES etc)	Mailed paper questionnaire	**X**	**X**	**X**	Partly at T1 and T2

**Triage**						
Patient	**Risk for functional loss**					
	ISAR-HP	Interview patient	**X**			
	MMSE (cognitive functioning)	Interview patient	**X**			
	NPI-Q (neuro-psychiatric functioning)	Phone interview informal caregiver	**X**			

* T0 = within 48 hours of hospital admission; T1 = 3 months after hospital admission; T2 = 12 months after hospital admission; MDS = Minimal Data Set; ISAR-HP = Identification Seniors At Risk (Hospitalized Patients); MMSE = Mini Mental State Examination; NPI-Q = Neuro-psychiatric Index;

**Table 2 T2:** Effect evaluation: Data collection of patient outcome variables

Patient outcome variables + instruments	Data collection methods	Data collection times			**Notes**:
		**T0**	**T1**	**T2**	

**Quality of life**					
SF-20	Interview patient	**X**	**X**	**X**	5 items part of MDS
EQ-5D (6D)	Interview patient	**X**	**X**	**X**	Part of MDS
SPF_IL	Interview patient		**X**	**X**	
**Physical performance**					
Katz -15	Interview patient	**X**	**X**	**X**	Part of MDS
Short Physical Performance Battery	"Do" test patient		**X**	**X**	
LAPAQ (physical activity)	Interview patient		**X**	**X**	
**Cognitive/psycho/social performance**					
NPI (neuro-psychiatric functioning)	Interview caregiver	**X**	**X**	**X**	
MMSE (cognitive functioning)	Interview patient	**X**	**X**	**X**	Short MMSE (T1 + T2)
Geriatric Depression Scale (depression)	Interview patient	**X**	**X**	**X**	
Global Deterioration Scale (dementia)	Phone interview inf. caregiver	**X**	**X**	**X**	
Loneliness scale Gierveld (social)	Interview patient	**X**			
**Intramural Residence**	Medical registries		**X**		
**(Re-)admission hospital/nursing home**	Interview patient/caregiver		**X**	**X**	
**Mortality**	Medical registries		**X**	**X**	

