### Objectives of the evaluation

This evaluation study entails an effect, process and cost evaluation of offered geriatric health care and has four main objectives. First of all, the study aims to determine to what extent the program, in comparison with other usual forms of geriatric care, leads to a retention in functioning and quality of life of at risk elderly, a reduction in the burden of care for the patient's primary informal caregiver, shorter lengths of hospital stay, and a reduction of 'wrong bed' problems as well as (re-) admission to hospitals, nursing homes and mortality. In addition, it will show the extent to which program care including a stay at a reactivation centre, leads to better functioning and quality of life of elderly patients in need of complex care. Secondly, the study aims to determine to what extent the triage instruments used in the program detect increased risk for functional loss and to determine how criteria for triage should be adjusted to optimally link the offered interventions to the needs of the individual elderly at risk. Thirdly, the evaluation will determine to what extent the program, in comparison with other, usual forms of geriatric care in the Netherlands, leads to a better structure and process of care. Finally, the cost-effectiveness of the program (both including and excluding a stay at a reactivation centre) will be determined in comparison with other usual forms of geriatric hospital care in the Netherlands.

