#### Power calculation and effect size

For the prospective cohort we expect to be able to collect a sample size of around 1100 patients in the intervention hospital (900 patients treated with the new intervention program and 200 patients treated with the new intervention program including a stay at the reactivation centre). Samples of minimal 500 to 600 patients will be collected in each of the two control hospitals. These estimations are based on the average number of elderly patients who are admitted to the different hospitals during our inclusion period of one year. According to preliminary pilot results on activities of daily living (Katz-15 ADL score), a population of n = 500 in the control hospitals will lead to around n = 300 persons analyzable at three months, whereas a baseline population of n = 1100 in the intervention hospital will lead to around 733 persons analyzable at three months. Using an effect size of 0.25 this will lead to a power of 95% [46]. Furthermore, to detect a smaller effect size (Cohen's D of 0.2), n = 1100 in the intervention hospital and n = 500 for the control hospitals will lead to a power of 83%. If possible, we will aim for a larger sample size in the control hospitals than the expected n = 500, (preferably 900), which will lead to N = 733 analyzable in the intervention hospital versus n = 600 analyzable in the control hospitals, with an effect size of 0.2 leading to a power of 95%. Abovementioned sample sizes are large enough to allow for reliable analysis per subgroup (e.g. subgroup of specific diagnoses) and sets of risk factors.

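### Table 2 gives only patient or caregiver interview as the source of (re)admission, a named objective, so up to 33–40% of patients could lack this outcome at three months

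*Protocol article*

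**What the plan says.** The first objective in the Protocol article (Objectives of the evaluation) includes a reduction in "re-) admission to hospitals, nursing homes and mortality".

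Table 2 sets a source for each outcome row by row. For "Re-)admission hospital/nursing home" it is "Interview patient/caregiver", at T1 and T2. For the adjacent rows, intramural residence (T1) and mortality (T1 and T2), it is "Medical registries".

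Four other places bear on the source:

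- **Data collection** says that further outcome information is drawn from patient files and hospital IT systems, partly retrospectively. It does not name readmission. The same section presents Tables 1 to 5 as the complete overview of outcomes and instruments.
- **Cost-effectiveness evaluation (table 5)** says that hospital and nursing-home use is collected centrally from standard files and cost diaries, together with questionnaires.
- **Table 5** times the hospital-registry items of the index stay mainly at discharge. For care use before and after that stay it lists only the patient interview and a mailed caregiver questionnaire.
- **Demographics** gives examples of registry data. Readmission is not among them.

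On expected follow-up, Data collection states: "Based on the pilot results we expect around 60% of patients analysable at 3 month follow up". The power section states that "a population of n = 500 in the control hospitals will lead to around n = 300 persons analyzable at three months" and that "a baseline population of n = 1100 in the intervention hospital will lead to around 733 persons analyzable at three months".

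**The concern.** A readmission can be read from a hospital's own records whether or not the patient can later be interviewed. An interview-based count covers only those for whom someone answers. In at-risk patients aged 65 or older, those who have died, are in hospital or have moved to a nursing home are plausibly the hardest to interview, so the outcome would tend to be missing where it is more likely to have occurred.

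Mortality would then be known for nearly everyone and readmission only for those reached. Two linked outcomes of the same objective would be reported in different populations, and the readmission risk would probably be too low. The documents also leave open whether the file-based collection described in the text was meant to cover this outcome.

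**Working it through.** **1. The plan's own figures.** The control ratio is 300/500 = 60.0%, which agrees with the stated 60%. The intervention ratio is 733/1100 = 66.6%. With a two-sided alpha of 0.05 (assumed; the article states none), 300 v 733 analysable gives power 95.4% at d = 0.25 and 83.1% at d = 0.20, and 600 v 733 gives 95.3% at d = 0.20. The plan states 95%, 83% and 95%. The analysable numbers are therefore those on which its power rests.

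**2. Share lacking the outcome with interviews alone and no proxy answers.**
- Control: (500 − 300)/500 = 40.0%
- Intervention: (1100 − 733)/1100 = 367/1100 = 33.4%
- Pooled over 1100 + 500: 567/1600 = 35.4%

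**3. Allowing for caregivers.** If caregivers answer for a share c of patients not reached, the missing share is (lost share) × (1 − c). The documents do not give c. The pilot offers a rough guide: 160 caregivers at three months and 200 at baseline per 500 patients, so 160/500 = 0.32 and 200/500 = 0.40. Applying these to patients not reached is an assumption.

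| c | Control | Intervention |
|---|---|---|
| 0 | 40.0% | 33.4% |
| 0.32 | 27.2% | 22.7% |
| 0.40 | 24.0% | 20.0% |

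**4. Illustration of the bias.** All risks here are assumed: a true risk of 25% in every hospital and 30% to 40% among those with the outcome missing. With missing share m, the observed risk is (0.25 − m × risk in missing)/(1 − m).

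| | Risk in missing 30% | Risk in missing 40% |
|---|---|---|
| Control, m = 0.400 | 21.7% | 15.0% |
| Intervention, m = 0.334 | 22.5% | 17.5% |
| Control, m = 0.240 | 23.4% | 20.3% |
| Intervention, m = 0.200 | 23.8% | 21.2% |

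Under these assumptions the understatement is about 2.5 to 10 points with no caregiver answers, and about 1 to 5 points with 40% caregiver cover.

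**5. Does the bias differ between hospitals?** The first two rows differ by 0.8 to 2.5 points, but this depends on two choices.
- It uses the control pair 300/500. The plan's preferred control sample is 900 with 600 analysable: 600/900 = 66.7%, practically the same as 66.6%. On that pair the difference all but vanishes.
- It fixes the same absolute risk among the lost in both groups. If the ratio of risk in lost to risk in responders is held at the control values instead (0.30/0.217 = 1.38 to 0.40/0.150 = 2.67), the difference is about 0.5 to 1.1 points even with 60% v 66.6%.

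**The case against.** The strongest reply is that the source is unclear rather than interview-only. The text describes file-based collection of outcomes and of hospital and nursing-home use, and intramural residence comes from registries. This stands in part. A reader might infer that readmission will be taken from interviews and nothing else, and the documents as a whole do not establish that. But neither text section names readmission as a file-based effect outcome, and the two tables that assign sources both rely on respondents for events after the stay.

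A reader might also infer that the outcome will be missing in 40% of all patients, including those who died. The documents do not support this:

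- A caregiver may answer, so a patient who is not reached is not automatically missing.
- The 40% is the pilot and control-hospital figure for patient data. The power section ties it to the Katz-15, not to an event that a proxy can report. The corresponding figure for the intervention hospital is 33%.
- The article does not say what share of those lost had died. That they include the deaths is plausible, but it is an inference.

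A third inference, that retention differs by hospital and so creates a spurious difference in readmission, is not established either. The retention figures are approximate planning numbers, and the preferred control sample has the same retention as the intervention hospital.

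Finally, registries of three hospitals miss admissions elsewhere and to nursing homes, so interviews have a proper place in this combined outcome. That is a reason to keep interviews as a supplement. It does not justify leaving registries out of the row.

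**Conclusion.** The point holds in a limited form. For a named objective, Table 2 lists only interviews, at odds with its treatment of the adjacent event outcomes and not reconciled with the text on file-based collection. If Table 2 is followed, up to 33% (intervention) to 40% (control) of patients could lack the outcome at three months. The figure falls to about 20–27% if caregivers answer for 32–40% of those not reached, which is an assumption. The article gives no retention figure for twelve months.

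The direction of bias, probably an understated risk, rests on the inference that readmission and death make an interview less likely. Its size cannot be derived from the documents; the 1 to 10 points above are illustrative. A difference in bias between hospitals is possible but not shown. The change is worth making because it is cheap relative to the information it protects.

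**What to change.** Reconcile Table 2 with the Data collection section, Table 5 and the Cost-effectiveness evaluation section, and name one primary source for hospital readmission:

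- Take hospital readmission up to T1 and T2 from the registries of the three hospitals for every enrolled patient, including those who died and those lost to interview.
- Use patient and caregiver interviews to add admissions to other hospitals and to nursing homes.
- Analyse hospital readmission in all enrolled patients.

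**Cost.** Registry data are already planned for the index stay and for mortality, so the systems are in use. The index-stay items are timed mainly at discharge, however, so the extraction has to be extended to twelve months, which is more than one extra field. Admissions elsewhere and nursing-home admissions would still rest on interviews, with the loss described above.
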